**Methods/design:**

The design is a multicentre, assessor-blinded clinical randomised controlled trial. A total of 166 patients with LDH (aged 18–65 years) were recruited from four centres and randomly assigned at a 1:1 ratio to two groups: the TCE group and the Tuina combined with the TCE group. Each group received three treatments over the course of 1 week for a total of 4 weeks. The primary outcome indicator was the Oswestry Disability Index, whereas the secondary outcome indicators were the Short Form of Quality of Life Scale, the Short-Form McGill Pain Questionnaire Scale, and gait analysis. Assessments were made before the treatment, at the end of the treatment, and at the third and sixth months’ follow-ups. Gait analysis was only used for comparison between the two groups before and after treatment, and did not involve follow-up. Adverse events occurring during the trial were faithfully recorded.

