## Methods

### Study design

This study is a multicentre randomised controlled clinical trial study conducted in four clinical centres (Figure 1). The Wuxi Hospital of Traditional Chinese Medicine is the main centre. The Yueyang Hospital of Integrative Medicine affiliated with the Shanghai University of Traditional Chinese Medicine, Wuxi Rehabilitation Hospital and the Wuxi Xinwu District Hospital of Traditional Chinese Medicine are the three subcentres. Patients were recruited through advertisements at each centre. Patients who met the inclusion criteria were randomly assigned to either the TCE group or the Tuina combined with TCE group at a 1:1 ratio. The trial consisted of a four-week intervention period and subsequent three- and six-month follow-up periods. Data were collected before treatment, after 4 weeks of treatment, and at 3 months and 6 months of follow-up. The outcome assessment indicators included the Oswestry Disability Index (ODI), Short Form of Quality of Life (SF-36) Scale, Short-Form McGill Pain Questionnaire (SF-MPQ) Scale and gait analysis, which was used only for efficacy evaluations before and after 4 weeks of treatment.

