### Statistical analysis

The data will be subjected to analysis by our team of professional statisticians, who will employ IBM SPSS Statistics V.27.0 for this purpose. To assess the normality of the data, the Kolmogorov–Smirnov test was used. The quantitative results were expressed in terms of the mean and standard deviation. The purpose of the primary and secondary outcome indicators was to assess the difference in efficacy between the two groups. Hypothesis testing was employed to this end. The chi-square test was used to ascertain the dissimilarities in baseline data between the two groups. The analysis of variance for repeated measures was utilised to examine the alterations in efficacy between the two groups before, during and after the intervention, as well as after the follow-up period. For confounding factors that were challenging to regulate or were not regulated prior to treatment, such as an imbalance between the groups prior to treatment, were treated as covariates, and logistic regression was employed to ascertain the variability of efficacy between groups and to eliminate the influence of these factors on efficacy. The data collection and data summarisation were meticulously examined to minimise data anomalies. In the event of missing data, the data were assumed to be missing at random, and multiple interpolation would be employed for analysis. Subjects who were excluded from the trial will be excluded from the data set. The level of statistical significance was set at 5% (*p* < 0.05), and 95% confidence intervals were employed as effect estimates.

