## Discussion

Tuina and TCEs are an important part of Chinese traditional medicine with a history of thousands of years, playing an important role in protecting the health of the Chinese people and accumulating a great deal of clinical experience. Although multicentre clinical studies have been published on the use of Tuina combined with TCEs for the treatment of LDH (16), they have not performed long-term observations of efficacy, and the TCE manoeuvre lacks specificity. Standardised clinical randomised controlled trials to validate whether Tuina combined with TCEs is necessarily superior to single TCEs for relieving dysfunction and pain in patients with LDH are also lacking. Consequently, a multicentre, large-sample, assessor-blinded clinical randomised controlled trial was designed. The short- and long-term improvement of dysfunction and pain in LDH patients with Tuina combined with TCEs was assessed by evaluating the health status of the subjects through multiple outcome indicators at preintervention, after 4 weeks of intervention, and at the third and at sixth months’ follow-up to validate that the combination therapy is more advantageous than the treatment with single TCEs.

This study was conducted at multiple clinical centres, offering several advantages. Firstly, this study used four clinical centres, divided into one main centre and three subcentres. This structure facilitated more opportunities for subject recruitment and ensured an adequate sample size. Secondly, the results can be independently verified and repeated in each subcentre to confirm the consistency and reliability of the main results, thus reducing bias and increasing credibility. Thirdly, the observations focused on the recovery of dysfunction in patients with LDH, which was assessed using gait analysis to assist in evaluating the recovery of walking function in addition to the ODI scale. Additionally, a follow-up period of up to 6 months was conducted following the four-week intervention to facilitate observation of the short- and long-term efficacy of Tuina combined with TCEs for LDH.

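### Gait is measured only twice, so the one longitudinal method stated amounts to a change-score test; adjust for baseline instead, and remove an on-treatment time point that the described schedule lacks

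*Protocol article*

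**What the plan says.** In the protocol article, the Statistical analysis section introduces its methods with the statement that "The purpose of the primary and secondary outcome indicators was to assess the difference in efficacy between the two groups". Two sentences later comes the only longitudinal method: "The analysis of variance for repeated measures was utilised to examine the alterations in efficacy". The time points for that comparison follow in the same sentence and are worded as "between the two groups before, during and after the intervention, as well as after the follow-up period". That sentence names no outcome and makes no separate provision for gait.

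The visit schedule is given three times, consistently:

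- Abstract, Methods/design: "Assessments were made before the treatment, at the end of the treatment, and at the third and sixth months’ follow-ups".
- Study design: "Data were collected before treatment, after 4 weeks of treatment, and at 3 months and 6 months of follow-up".
- Discussion: "at preintervention, after 4 weeks of intervention, and at the third and at sixth months’ follow-up".

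Gait has a shorter schedule. The Abstract says "Gait analysis was only used for comparison between the two groups before and after treatment, and did not involve follow-up", and Study design refers to "gait analysis, which was used only for efficacy evaluations before and after 4 weeks of treatment".

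Covariates appear in the Statistical analysis section only as a remedy for confounders that were not controlled, such as a baseline imbalance, and the method named for that adjustment is logistic regression.

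**The concern.** Two things do not fit together. First, the analysis sentence names a level during the intervention, and none of the three schedule statements contains an assessment between baseline and 4 weeks. In a repeated-measures ANOVA the time levels define what the group-by-time test asks, so the sentence and the schedule should agree.

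Second, gait is a secondary outcome, and the Introduction lists it beside dysfunction and pain among the things the combined therapy is expected to improve. Its two-visit schedule is clear. When the only longitudinal method in the plan is applied to two visits, it gives a comparison of mean change. That is valid but less precise than a comparison adjusted for the baseline value, which is already collected. The adjustment the plan does offer would not supply it, because it depends on imbalance and uses a model for binary outcomes, while gait measures such as step length and cadence are quantitative. What is at stake is precision on gait, and clarity about which time points enter the analysis of the three scales.

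**Working it through.** **Step 1. Time levels named against time levels scheduled.**

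| Outcome | Scheduled | Named in the analysis sentence but not scheduled |
|---|---|---|
| ODI, SF-36, SF-MPQ | baseline, 4 weeks, 3 months, 6 months | during the intervention |
| Gait | baseline, 4 weeks | during the intervention; also follow-up, if the general sentence is read to cover gait |

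A two-group repeated-measures ANOVA can be fitted with four levels or with two. Only the on-treatment level has no data.

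**Step 2. What the model tests for gait.** With two visits, the group-by-time interaction compares the mean of (4-week value minus baseline) between arms. It is therefore the two-sample test on change scores.

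**Step 3. Variance of the two comparisons.** Let the standard deviation be σ at both visits and in both arms, and let r be the within-patient correlation between baseline and 4-week gait. The documents give no r, so it is an assumption here. Per patient:

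- Change score: σ² + σ² − 2rσ² = 2(1 − r)σ².
- 4-week value adjusted for baseline: (1 − r²)σ².
- Ratio, adjusted to change: (1 − r²) / [2(1 − r)] = (1 + r)/2.

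| Assumed r | Change-score variance | Adjusted variance | Ratio | Reduction |
|---|---|---|---|---|
| 0.5 | 1.00σ² | 0.75σ² | 0.75 | 25% |
| 0.7 | 0.60σ² | 0.51σ² | 0.85 | 15% |

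The ratio is below 1 for every r below 1. In terms of patients, a change-score analysis of all 166 has the precision of an adjusted analysis of about 166 × 0.75 = 124.5 patients at r = 0.5, or 166 × 0.85 = 141.1 at r = 0.7.

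**Step 4. The three scales.** With baseline as one of four time levels, the group-by-time test includes the change from baseline to 4 weeks. If the levels are cut to 4 weeks, 3 months and 6 months, the group-by-time test asks only whether the between-arm difference varies across those visits. A benefit of constant size would not show in it. With those three levels, baseline therefore has to enter as a covariate, and the effect to report is the between-arm difference at each visit.

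**Step 5. The plan's own figure.** The stated 74 per group rests on 4-week ODI means and a standard deviation, and does not use the time levels. With a difference beyond the margin of |14.53 − 19.73 + 4| = 1.2, SD 2.60, two-sided 5% and 80% power, and the denominator squared, the calculation gives 73.69, rounded up to 74. Nothing here changes it.

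**The case against.** The strongest case on the other side is that this comes down to one loose word and a preference. Three schedule statements agree, and the Outcomes section uses a similar phrase with *during* attached to the follow-up period, so the word in the analysis sentence is probably misplaced. An analyst with the protocol in hand would not look for a mid-treatment value. That stands, and it is why the word is treated here as editorial. Figure 4, the schedule figure, is not shown. A mid-treatment visit there cannot be wholly excluded, but it would conflict with the three text statements.

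It can also be said that the ANOVA sentence does not mention gait, that the specific restriction of gait to two visits governs the general sentence, and that listing time levels by outcome is normal content for an analysis plan. This too largely stands. That the ANOVA applies to gait is an inference from its being the only longitudinal method stated for the outcomes. The change-score test is also valid, and the gain from adjustment depends on an assumed correlation. It remains true, however, that the document names no baseline-adjusted comparison suited to gait.

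A reader might go further and infer three things that the documents do not support:

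- **That the efficacy analysis cannot be run as written.** It can, on four visits for the scales and two for gait.
- **That the empty on-treatment level might be filled by imputation.** The plan imputes missing data. A visit that was never scheduled is not missing, and with no observed value in any patient there is nothing to impute from.
- **That the trial makes a long-term gait claim it cannot support.** The Abstract excludes gait follow-up, and the Discussion ties short- and long-term improvement to dysfunction and pain.

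**Conclusion.** The point holds in a limited form. The on-treatment time point in the analysis sentence is inconsistent with the schedule as described in the text and should be reconciled with it. Removing it alters no visit, dataset, sample size or result.

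The substantive part is an inexpensive gain in precision for gait. The stated method reduces to a change-score test, and a baseline-adjusted 4-week comparison would have 0.75 of its variance at r = 0.5 and 0.85 at r = 0.7. These figures assume equal standard deviations at both visits and in both arms, a linear relation with baseline and complete gait data. With unequal standard deviations the ratio differs, but apart from the one degree of freedom spent on the slope the adjusted comparison is still no less precise, because it estimates the baseline slope that the change score fixes at 1. This is a matter of efficiency; no bias in the planned comparison is alleged.

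**What to change.** 1. **Gait:** state that the 4-week value of each gait measure is compared between arms in a linear model with that measure's baseline value as covariate, whether or not the arms look imbalanced.
2. **Analysis sentence:** delete *during*. If Figure 4 does show an on-treatment assessment, reconcile the figure, the schedule statements and the analysis sentence instead.
3. **ODI, SF-36 and SF-MPQ:** name the time levels. If they are 4 weeks, 3 months and 6 months, state that the baseline value enters as a covariate and that the between-arm difference at each visit is the effect of interest, so that dropping baseline from the levels does not lose the treatment effect.

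The cost is a few sentences. Items 1 and 3 specify the analysis and so go beyond editing; they should be fixed before outcome data are examined by arm. All the measurements needed are already scheduled, and no visit or patient is added.

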### Intervention

This study is a multicentre clinical trial. To ensure the consistency and standardisation of treatment modalities across all clinical centres, therapists from the main centre conducted training sessions for therapists from the subcentres. The objective of these sessions was to standardise the Tuina treatment protocols and the TCE movement, and to treat patients in accordance with the interventions outlined in the study protocol. Prior to intervening with patients, therapists at subcentres must undergo training and evaluation at the main centre. They are not qualified to intervene until they have met the training requirements. Furthermore, to mitigate bias in the treatment of patients by different therapists, only one Tuina therapist and one TCE therapist were appointed to conduct the intervention at each clinical centre. TCE therapists must have at least 10 years of experience teaching TCEs.

To ensure that each subject can master the movement essentials of TCEs, a TCE treatment manual was issued to the subjects before the intervention. A comprehensive introduction to the movement essentials and precautions of TCEs through offline lectures and online video teaching mode followed. The therapist maintained a treatment log for each subject and recorded the subject’s progress and any issue that arise. If a subject has not completed the prescribed treatment within the allotted time, the therapist will contact the subject by phone to ensure that the subject has met the standard treatment volume.

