### Primary outcome

The ODI scale, which consists of 10 items in 3 dimensions, namely pain, individual functioning and overall personal functioning, was used as a comparison of efficacy before and after treatment and between groups (28). The maximum score was 50; the higher the score, the higher the degree of dysfunction of the patients.

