### Secondary outcome

The SF-36 Scale evaluates health in eight dimensions, including physical functioning, general mental health and social functioning, and higher scores indicate better health (29). Each dimension was rated with a maximum of 100 points and a minimum of 0 points.

The SF-MPQ Scale includes three parts: pain rating index (PRI), (VAS) and present pain intensity (PPI) (30). The PRI assesses the patient’s emotional and sensual experiences of pain. The VAS provides a straightforward visual representation of the patient’s pain level. The PPI determines the intensity of the patient’s current pain on a six-point scale (0–5).

Gait analysis is the process of collecting patient information using a wearable 3D gait analyser. Gait analysis encompasses a range of patient data, including step length, cadence, stride length and double support phase. This information is utilised to assess the patient’s motor function and musculoskeletal rehabilitation status (31).

After all the relevant items were confirmed by the patients themselves, the total score reflecting the degree of low back and leg pain in each period was calculated cumulatively by a specialised statistician, and the results were used for pre- and post-treatment comparisons as well as comparisons between groups.

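### The covariate-adjusted efficacy comparison is assigned to logistic regression, although no binary efficacy endpoint is defined and the trial is sized on mean ODI

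*Protocol article*

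**What the plan says.** All of the following is in the protocol article.

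- Main efficacy model (Statistical analysis): "The analysis of variance for repeated measures was utilised to examine the alterations in efficacy between the two groups", across the visits before, during and after treatment and at follow-up. Summaries match this: "The quantitative results were expressed in terms of the mean and standard deviation".
- Adjusted efficacy model (same section): "logistic regression was employed to ascertain the variability of efficacy between groups and to eliminate the influence of these factors on efficacy". Those factors are confounders that were hard to control, or left uncontrolled, at the start, "such as an imbalance between the groups prior to treatment, were treated as covariates".
- Primary outcome (Primary outcome): the ODI total. "The maximum score was 50; the higher the score, the higher the degree of dysfunction of the patients".
- Secondary outcomes (Secondary outcome): the SF-36, of which "Each dimension was rated with a maximum of 100 points and a minimum of 0 points"; the SF-MPQ, made up of PRI, VAS and a PPI item scored 0 to 5; and gait measurements such as step length and cadence.
- Sample size (Sample size calculation): means of 14.53 and 19.73 ODI points after 4 weeks, SD 2.60, margin -4, alpha 0.05, beta 0.2, giving 74 per group.

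**The concern.** Logistic regression models a categorical dependent variable, usually a yes/no result. The protocol defines no such efficacy result: no responder, no cure or effective rate, and no threshold on any scale. The adjusted analysis therefore cannot be run on the ODI as described. Someone would first have to choose a cut-off that the protocol does not contain.

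The result would also be on the wrong scale. The trial asks whether mean ODI differs by more than a stated number of points. An odds ratio from a dichotomised ODI does not estimate that quantity, so the adjusted result could neither confirm nor correct the unadjusted one.

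The covariates raise a second, smaller question. None is named, and the only example given is a between-group imbalance before treatment, which is known only once baseline data are in hand. Whether and how the comparison is adjusted is then not settled in advance.

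**Working it through.** **1. Is the trial sized on a continuous outcome?** Inputs from the Sample size calculation section: difference 14.53 - 19.73 = -5.20; margin -4; difference beyond the margin -5.20 + 4 = -1.20; SD 2.60; Z values 1.960 and 0.842.

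n per group = 2 × (1.960 + 0.842)² × 2.60² / 1.20² = 73.7, rounded up to 74.

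The stated figure reproduces as a two-sided 5%, 80% power comparison of mean ODI. It needs the squared denominator. The formula as printed lacks the square and would give -88.4, which is a separate matter.

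**2. Does any outcome fit the named model?** The outcome definitions set against the model:

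| Outcome | Type as defined | Binary endpoint or cut-off given? |
|---|---|---|
| ODI total (maximum 50) | numeric | no |
| SF-36 dimensions (0–100) | numeric | no |
| PRI, VAS | numeric | no |
| PPI (0–5) | six-point ordinal | no |
| Gait measurements | numeric | no |

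An ordinal logistic model could be considered for the PPI, but the text names neither that item nor that model.

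**3. Can the odds ratio be related to the ODI difference?** Take the protocol's means and SD of 2.60, and assume normal scores with that SD in both arms. The difference is 5.20 / 2.60 = 2 SD. The cut-offs below are assumptions, since the document has none.

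- Cut-off midway between the means (17.13): proportions below it are 0.841 (combined arm) and 0.159 (TCE arm). Odds ratio = (0.841/0.159) / (0.159/0.841), about 28.
- Cut-off 1 SD higher (19.73): proportions 0.977 and 0.500. Odds ratio = (0.977/0.023) / 1, about 43 with unrounded proportions.

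The same 5.2-point difference gives two quite different odds ratios. Likewise, a margin of 4 ODI points has no fixed equivalent on the odds-ratio scale.

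**4. What could a linear adjusted model offer?** For illustration, take the excess of 1.2 points, SD 2.60 and 74 per group. The baseline-to-week-4 correlation r is assumed, as the document gives none.

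Power = Φ(1.2 / [2.60 × √(2/74) × √(1 - r²)] - 1.96) = Φ(2.807 / √(1 - r²) - 1.96)

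| r | Power |
|---|---|
| 0 | 80% |
| 0.3 | 84% |
| 0.5 | 90% |
| 0.7 | 98% |

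These gains are relative to a comparison of post-treatment scores alone, not to the planned repeated-measures analysis.

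**The case against.** The strongest reply is that logistic regression is not the main analysis. Repeated-measures analysis of variance carries the efficacy comparison and suits numeric scores. This stands, and it limits the point to the adjusted comparison. It does not rescue that comparison, because the text names the model and a separate analysis plan naming another would contradict the article.

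A reader might infer more than the document supports, in four ways.

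- **That dichotomising would cost a large part of the 80% power.** That follows only if the 1.2-point excess over the margin is treated as the whole treatment effect. On the protocol's own assumptions the arms differ by 2 SD. With the midway cut-off and 74 per group, z = (0.841 - 0.159) / √(2 × 0.841 × 0.159 / 74), about 11, so a test of no difference would have power near 100%. The harm is a result on the wrong scale, not a demonstrated loss of power.
- **That covariates enter only when a baseline test is significant.** The article does say "The chi-square test was used to ascertain the dissimilarities in baseline data between the two groups", but it does not make that test the trigger, and imbalance is given only as an example. The lack of a named test for continuous baseline variables may be filled by an analysis plan.
- **That baseline ODI is ignored.** The repeated-measures analysis includes the pre-treatment measurement. What is missing is its use as a covariate fixed in advance in the adjusted model.
- **That centre is wrongly left out.** The article says that "only one Tuina therapist and one TCE therapist were appointed to conduct the intervention at each clinical centre", which makes centre a sensible covariate, but nothing excludes it and a full covariate list is commonly left to an analysis plan.

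**Conclusion.** The point holds for the covariate-adjusted efficacy comparison. The stated model does not match the outcomes as defined, requires a cut-off the protocol does not set, and yields an estimate that cannot be compared with the mean ODI difference or the 4-point margin. The adjustment is also not fixed before baseline data are seen; the text does not suggest that covariates would be chosen on outcome data.

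This should be fixed, but it does not undermine the main analysis. No power loss is claimed. The odds ratios of 28 and 43 rest on normality, a common SD of 2.60 and assumed cut-offs. The 84% to 98% range rests on assumed correlations and is only illustrative.

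**What to change.** Replace the logistic regression with a linear model for the ODI and the other numeric scores: either ANCOVA at week 4 or a linear mixed model across visits. Gait is measured only before and after treatment, so ANCOVA at week 4 suits it. Include the baseline value of the outcome as a fixed covariate whether or not an imbalance is observed; centre may be added. Report the adjusted mean difference with its 95% CI, so that it can be set beside the unadjusted difference and the margin.

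If logistic regression is truly intended, define the responder endpoint and its cut-off in advance and label it a secondary analysis.

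The cost is wording only. No new data are needed, because baseline scores and centre are already recorded. The baseline covariate uses 1 degree of freedom and centre, with four sites, uses 3.

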### Recruitment

Subjects were recruited at each subcentre through a variety of channels, including printed advertisements, flyer distribution, telephone inquiries, and public announcements on the hospital’s WeChat public website. Each subject participating in the trial must meet the inclusion criteria. Subjects who meet any of the exclusion criteria subject will be excluded. The principal investigator will not request that the subject sign an informed consent form until the subject has had sufficient opportunity to understand the nature of the trial and to agree to participate in it.

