### Randomisation, allocation concealment and blinding

The random sequence was generated by a statistician independent of the study through a central randomisation system. The random numbers and group assignments were provided to the independent researcher through the central randomisation system. This researcher was not involved in any other aspect of the trial. The physician only obtained the grouping information from this independent researcher by telephone before the treatment. The central randomisation system had strict limitations on the permissions granted, and only the supervisory staff had access to these documents. This procedure ensured adequate concealment of the randomisation. The study was not blinded to the patients and therapists, but it was blinded to the evaluators. This evaluator was independent of this study. The TCEs therapists were separated from the Tuina therapists, and neither group was aware of the grouping of the patients. Patients were not allowed to interact with the therapist beyond general counseling about their health status at each session.

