### Quality control

Prior to the implementation of the trial, ensuring that all study personnel received a uniform, centralised training was necessary to achieve an accurate understanding and mastery of the various criteria for cases (diagnosis, inclusion, exclusion, exclusion, shedding and termination criteria), the technical protocols of the treatment, the observational indicators and the scoring criteria. The case report form (CRF) was completed in its entirety and in accordance with the prescribed specifications, with no arbitrary alterations. Furthermore, observations of the same subject were recorded by the same individual whenever feasible.

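### The rule that removes excluded subjects from the data set does not define them, and as written it permits deletion of randomised patients

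*Protocol article*

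**What the plan says.** Two adjacent sentences in the protocol article, Statistical analysis, govern patients with incomplete data. The first is: "In the event of missing data, the data were assumed to be missing at random, and multiple interpolation would be employed for analysis". I read interpolation as multiple imputation. The second is: "Subjects who were excluded from the trial will be excluded from the data set". It carries no condition, and the article names no analysis set that would limit it.

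Two other places bear on what *excluded* means:

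- Recruitment uses the word for eligibility: "Subjects who meet any of the exclusion criteria subject will be excluded".
- Quality control gives the list of criteria on which staff are trained: "diagnosis, inclusion, exclusion, exclusion, shedding and termination criteria". Exclusion appears twice, and shedding (dropout) and termination are listed separately.

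On blinding, the article says: "The study was not blinded to the patients and therapists, but it was blinded to the evaluators".

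**The concern.** A randomised comparison is protected only while patients are analysed in the groups to which they were assigned. If patients can be taken out of the data set after randomisation, on grounds the article does not state, the remaining groups may differ for reasons other than treatment. Patients know their treatment and only one arm receives Tuina, so the reasons for removal could differ between arms. Blinding the assessors does not protect against this.

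There is also a practical gap. A patient who is withdrawn and has no later ODI could be imputed under one sentence or deleted under the next. The population for the primary comparison is then not fixed, and the choice could be made after the data are known.

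**Working it through.** **1. Which subjects does the sentence cover?**

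- *Eligibility only.* This is the sense used under Recruitment. Such subjects are never randomised and have no outcome data to remove, so the sentence would do nothing to the comparison.
- *Removal after randomisation.* The sentence stands among the analysis rules, directly after missing data, and Quality control names exclusion a second time next to dropout and termination. On this reading the sentence has an effect: randomised patients are deleted.

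The second reading fits the text better. It is not certain, because the repeated word may be a slip and the list gives neither timing nor grounds.

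**2. Does it clash with imputation?** If excluded and shed subjects are strictly separate, dropouts can be imputed and excluded subjects deleted without conflict. The rules collide only if *excluded* also covers withdrawn patients, and the article does not say.

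**3. The plan's own figure.** Inputs from Sample size calculation: means 14.53 and 19.73, σ = 2.60, Δ = −4, two-sided α = 0.05, β = 0.2.

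- Planned difference: 19.73 − 14.53 = 5.20. Excess over the margin: 5.20 − 4 = 1.20.
- n = 2(1.960 + 0.842)² × 2.60² / 1.20² = 73.7, rounded up to 74 per group. The stated 74 is reproduced with the denominator squared. The printed formula omits the square, which is a separate matter.
- The total of 166 is 83 per group. It matches 74/0.90 = 82.2, rounded up to 83, but 10% is my inference. The article states no loss rate.

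**4. Power.** For the same margin test:

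| Per group | Power |
|---|---|
| 83 | 84.5% |
| 74 | 80.2% |
| 70 | 78.0% |
| 66 | 75.5% |

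Even deletion of 18 of 166 (10.8%) still leaves 80% power. The issue is bias more than precision.

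**5. Bias.** Suppose a share *f* of one arm is deleted and its mean ODI is *k* SD worse than that of the remaining patients, whose mean is *m*. The full-arm mean is (1 − f)m + f(m + kσ) = m + fkσ, and the reported mean is *m*. The shift is therefore f × k × 2.60. Both *f* and *k* are assumptions. Cells give ODI points and, in brackets, the share of 1.20.

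| f | k = 0.5 | k = 1.0 | k = 1.5 |
|---|---|---|---|
| 5% | 0.065 (5.4%) | 0.130 (10.8%) | 0.195 (16.3%) |
| 10% | 0.130 (10.8%) | 0.260 (21.7%) | 0.390 (32.5%) |
| 15% | 0.195 (16.3%) | 0.390 (32.5%) | 0.585 (48.8%) |

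A higher ODI is worse. Deleting such patients from the combination arm overstates its benefit, and deleting them from the TCE arm understates it. With equal *f* and *k* in both arms the shifts cancel.

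**The case against.** The strongest reply is that the only place where the article explains exclusion concerns eligibility, so the sentence may describe people who never entered the trial. The criteria named under Quality control, and the analysis sets, may be defined in the full protocol. This stands in part: it makes the harm conditional, and the absence of those definitions from an article is not itself a fault. It does not rescue the sentence, because the article states the rule outright and an eligibility-only rule would have nothing to delete.

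Three stronger readings are tempting, and the documents support none of them:

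- *That the deletion rule contradicts the imputation plan.* Exclusion and shedding are listed separately, so the two rules can coexist. What the text supports is that the boundary between them is undefined.
- *That exclusions will probably fall on poor responders in the combination arm.* No section links exclusion to pain, intolerance or response, or gives a rate by arm. Lack of blinding makes differential removal possible, not established. The Randomisation, allocation concealment and blinding section also says the therapists did not know the grouping, so the patients' own knowledge is the firmer ground.
- *That the plan budgets for 18 losses and the benefit would be inflated by 0.56 points.* The arithmetic is right: with 9 of 83 combination patients deleted at the TCE mean, the true difference is 5.20 × 74/83 = 4.64, and 5.20 − 4.64 = 0.56. But the article states no such allowance, the loss is placed in one arm only, and the deleted patients are 5.20/2.60 = 2 SD worse than the rest of their arm. It is an extreme illustration, and even then 4.64 exceeds the margin of 4.

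**Conclusion.** The concern holds in a conditional form. The sentence is exact and unconditional, its key term is undefined, and its likelier meaning permits removal of randomised patients. It also leaves the handling of withdrawn patients open. It does not show that the randomised comparison will be broken: if only subjects excluded before randomisation are meant, the rule is harmless and the article need only say so.

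On the assumptions shown (one-sided deletion of 5% to 15%, 0.5 to 1.5 SD worse, SD 2.60), the shift is 0.07 to 0.59 ODI points, in either direction. At 10% and 1 SD it is 0.26 points. These figures are small against the planned difference of 5.20, but they matter because the sample size rests on an excess of only 1.20 over the margin.

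**What to change.** Replace the sentence with a rule on these lines: the primary analysis includes every randomised patient in the group assigned, and missing outcomes are handled by the multiple imputation already planned. Limit *excluded* to subjects who were never randomised. Any analysis set that drops randomised patients is reported as a sensitivity analysis only.

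The change is one of analysis wording and should be made before the database is locked. It needs no additional patients. The downside is that the estimated benefit may become slightly less favourable.
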